## Abstract

**Background:**

Evidence is limited on the effectiveness of mobile health programs which provide stage-based health information messages to pregnant and postpartum women. Kilkari is an outbound service that delivers weekly, stage-based audio messages about pregnancy, childbirth, and childcare directly to families in 13 states across India on their mobile phones. In this protocol we outline methods for measuring the effectiveness and cost-effectiveness of Kilkari.

**Methods:**

The study is an individually randomized controlled trial (iRCT) with a parallel, partially concurrent, and unblinded design. Five thousand pregnant women will be enrolled from four districts of Madhya Pradesh and randomized to an intervention or control arm. The women in the intervention arm will receive Kilkari messages while the control group will not receive any Kilkari messages as part of the study. Women in both arms will be followed from enrollment in the second and early third trimesters of pregnancy until one year after delivery. Differences in primary outcomes across study arms including early and exclusive breastfeeding and the adoption of modern contraception at 1 year postpartum will be assessed using intention to treat methodology. Surveys will be administered at baseline and endline containing modules on phone ownership, geographical and demographic characteristics, knowledge, practices, respectful maternity care, and coverage for antenatal care, delivery, and postnatal care. In-depth interviews and focus group discussions will be carried out to understand user perceptions of Kilkari, and more broadly, experiences providing phone numbers and personal health information to health care providers. Costs and consequences will be estimated from a societal perspective for the 2018–2019 analytic time horizon.

**Discussion:**

Kilkari is the largest maternal messaging program, in terms of absolute numbers, currently being implemented globally. Evaluations of similar initiatives elsewhere have been small in scale and focused on summative outcomes, presenting limited evidence on individual exposure to content. Drawing upon system-generated data, we explore linkages between successful receipt of calls, user engagement with calls, and reported outcomes. This is the first study of its kind in India and is anticipated to provide the most robust and comprehensive evidence to date on maternal messaging programs globally.

**Trial registration:**

Clinicaltrials.gov, 90075552, NCT03576157. Registered on 22 June 2018.

**Electronic supplementary material:**

The online version of this article (10.1186/s13063-019-3369-5) contains supplementary material, which is available to authorized users.

## Background

Despite the proliferation of mobile health (mHealth) programs, evidence on their effectiveness is limited [1, 2]. mHealth solutions which provide stage-based health information messages to pregnant and postpartum women have been shown to increase knowledge, as well as the utilization of antenatal care (ANC), skilled birth attendance (SBA), and childhood immunization rates in Malawi and Zanzibar [1, 3, 4]. However, efforts to compare and/or generalize these findings are limited by the paucity of data and the quality of evaluations and evidence reporting. To date, none of the summative evaluations have reported data on exposure—defined as a function of whether users receive content (technological performance) and how they engage with that content (behavioral performance)—thus hindering efforts to understand the casual pathways between program inputs and the summative outcome measures observed [3, 5, 6].

Despite evidence limitations, maternal messaging programs are among the few examples of mHealth programs which have been successfully scaled. In four countries globally, programs exist with over one million beneficiaries: *Aponjon* in Bangladesh, *mMitra* and *Kilkari* in India, *Wazazi Nipendeni* in Tanzania, and *MomConnect* in South Africa [7]. As these programs transition from donor funding to full integration with public sector health services, renewed calls to generate evidence on their effectiveness and value for money are emerging.

In India, the Kilkari program is an outbound service that delivers weekly, stage-based audio messages about pregnancy, childbirth, and childcare directly to families on their mobile phones, starting from the second trimester of pregnancy until the child is one year old. Initiated in Bihar in 2012, Kilkari has been scaled to 13 states across India with support from Ministry of Health and Family Welfare (MOHFW) at the national level, National Health Missions (NHM) at the state level, and an alliance of donors (Bill and Melinda Gates Foundation, US Agency for International Development (USAID), Barr Foundation, and UK Department for International Development (DFID)). In the preceding 33 months, Kilkari has delivered pre-recorded audio content to an estimated 8.3 million users—making it the largest maternal messaging initiative underway globally.

In this protocol paper, we outline proposed efforts to measure the effectiveness and cost-effectiveness of Kilkari through an individually randomized controlled trial (iRCT) in four districts of Madhya Pradesh (MP). To complement summative outcome measures, we describe qualitative research which will aim to understand user perceptions of mobile messaging as well as responses to program content, access to mobile phones, and, more broadly, experiences providing phone numbers and personal health information to health care providers in both MP and Rajasthan. Sub-studies to develop validated phone survey tools for the measurement of essential newborn care practices and respectful maternity care (RMC) during pregnancy and childbirth are described in brief here and greater detail elsewhere. Also, described elsewhere are planned secondary analyses of Kilkari data from 13 states where deployments are also underway which will use big data analytics, including machine learning, to explore data quality and develop predictive algorithms for measuring listening levels.

## Methods

### Hypothesis, aims, and objectives

#### Primary research question

Does exposure to mobile health information messages during pregnancy and postpartum improve infant feeding and family planning practices in MP, India?

#### Primary research hypothesis

Exposure to Kilkari messages on infant feeding will correspond to a 5% increased prevalence in the reported practice of exclusive breastfeeding for infants 0–6 months of age and use of modern contraceptive methods at 1 year postpartum between intervention and control arms. The control arm is expected to have a prevalence of 58% for the exclusive breastfeeding indicator and based on the recent NFHS data for MP.

##### Study aim 1. Generate evidence on the effectiveness of Kilkari in four districts of MP

Objective 1a. Measure changes in reproductive maternal newborn and child health (RMNCH) knowledge, practices, and care-seeking in the intervention arm compared to the control armObjective 1b. Measure the reported prevalence of disrespect and abuse during pregnancyObjective 1c. Develop validated phone survey tools for measuring RMC, essential newborn care, and infant feeding practicesObjective 1d. Administer a phone survey to measure RMC, as well as reported infant feeding and essential newborn care practices

##### Study aim 2. Identify factors which could impede the uptake of Kilkari and exposure to health information messages

Objective 2a. Measure reported prevalence of disrespect and abuse among women with a birth outcome in the preceding 1–4 months in four districts of MPObjective 2b. Identify barriers/facilitators for pregnancy and birth registration of pregnant women and enrolment of their mobile phone numbers in the Maternal and Child Health Tracking System (MCTS), including to the sharing of personal data and mobile phone numbers in MP and Rajasthan, India

##### Study aim 3. Understand the factors underpinning successful receipt of calls in four districts of MP

Objective 2a. Determine what proportion of calls are received by Kilkari usersObjective 2b. Determine predictors for exposure to Kilkari content based on user characteristics, Interactive Voice Response (IVR), and call center records

##### Study aim 4. Determine whether users are listening to calls received in four districts of MP

Objective 3a. Examine user perceptions of mobile messaging and use of data for program design and decision-making in MP, IndiaObjective 3b. Measure exposure to Kilkari content based on successful delivery of calls (technological performance) and user engagement (behavioral performance) in four districts of MP

##### Study aim 5. Determine the value for money of Kilkari in four districts of MP

Objective 5a. Measure economic costs from a societal perspective to start-up and support ongoing implementation of KilkariObjective 5b. Measure incremental changes in the coverage of services and uptake of recommended RMNCH practices among women exposed to Kilkari messages vs those not exposed in four districts of MPObjective 5c. Determine the incremental cost per disability adjusted life years (DALYs) averted of exposure to Kilkari compared to a null scenario of no messagesObjective 5d. Conduct sensitivity analyses on key drivers of costs and effects

### Intervention description and enrollment

Kilkari is comprised of 90 min of content delivered through 72 once weekly voice calls: 24 during pregnancy, 24 within the first 6 months postpartum, and 24 from 6 to 12 months postpartum. An estimated 16% of content is comprised of health information on family planning, 13% on infant feeding, 11% on child immunizations, 10% on pregnancy care, 8% on child malnutrition, 7% on diarrhea, and 7% on postnatal care (Table 1).

**Table 1 Tab1:** Messaging duration in seconds by content area

Content area	Duration in seconds (Topic + content)	
Family planning	874	16%
Infant feeding: breastfeeding, complementary feeding	686	13%
Child immunizations	568	11%
Pregnancy care: ANC, rest, birth preparedness, danger signs, Tetanus toxoid	559	10%
Child malnutrition, anemia, growth monitoring	455	8%
Diarrhea	379	7%
Postnatal care: newborn danger signs, cord care, hypothermia	370	7%
Child health, *Rashtriya Bal Swasthya Karyakram* (RBSK)	299	6%
Delivery: institution, pre-term, home, ambulance	297	6%
Maternal nutrition/anemia/IFA	235	4%
Safe drinking/hygiene/hand washing	167	3%
*Janani Shishu Suraksha Karyakaram* (JSSK)	159	3%
Pneumonia	130	2%
Childhood diseases	83	2%
Test for pregnancy	72	1%
Malaria	66	1%
Total messaging time in seconds	5399	100%

In the 13 states where Kilkari implementation is ongoing, pregnant woman or postpartum women’s data are entered into one of two health information systems registries: maternal and child health tracking system (MCTS) or reproductive and child health (RCH) system. Data, including mobile phone numbers, are collected in paper registers by frontline health workers, including auxiliary nurse midwives (ANMs) and accredited social health activists (ASHAs), and entered by data entry operators (DEOs) into the government’s electronic health records system—either MCTS or RCH system depending on the state. Data are then sent from there to the MOTECH system. Before the data are accepted by MOTECH, the system automatically runs validations to check that the mobile numbers are in the correct format, locations match location masters in the MOTECH database, and last menstrual period (LMP) and date of birth are within the Kilkari timeframe. The MOTECH system then determines the schedule for Kilkari messages based on the LMP or delivery date and the MOTECH engine provides the list of phone numbers (clients) to be called each day to the IVR system, which then calls the numbers and plays the appropriate pre-recorded message.

For the purposes of this intervention, mobile numbers will be collected directly by the research team for randomization. Pregnant and postpartum women randomized to receive Kilkari messages will receive messages from their enrollment in pregnancy through to 12 months postpartum. Women enrolled to the comparison arm (status quo) will not receive messages.

### Theory of change

Figure 1 depicts a theory of change for Kilkari’s impact on health outcomes specific to immediate and exclusive breastfeeding. This theory of change builds off of frameworks proposed by Kimani-Murage et al. [8] and Rollins et al. [9] for assessing factors affecting the actualization of breastfeeding recommendations.

**Fig. 1 Fig1:**
[figure not shown]
Theory of change for assessing the impact of Kilkari

### Study design

The study is an individually randomized controlled trial (iRCT) with a parallel, partially concurrent, and unblinded design.

### Participants and study setting

Study participants will include pregnant and postpartum women from four districts (Rajgarh, Rewa, Hoshangabad, Mandsaur) of MP where Kilkari implementation has not yet occurred. Additional qualitative research specific to MCTS/ RCH will be carried out in two districts (Pali and Sikar) of Rajasthan. In both states, district selection was made by the MOHFW with inputs from the implementing partner BBC Media Action.

The study setting in MP is characterized by disparities in access to education, mobile phones, and health services by gender and geographic location (rural/urban). With a population of over 75 million, MP is home to over 20% of India’s population. MP ranks as one of the worst performing states in India economically (gross domestic product per capita of $1100 USD versus $1709 nationally) and in terms of health outcomes, particularly with regard to child nutrition. In 2015, only 35% of children were breastfed within one hour of birth and 58% of children exclusively breastfed until 6 months [10]. One in four children aged under 5 years were wasted (weight-for-height), and 42% were stunted (height-for-age) [10]. While over half of pregnant women attended ANC in the first trimester, only 36% received the recommended four ANC visits [10]. Rates of institutional delivery were high with over 81% of women reportedly delivering in a health facility in 2015, and yet only 18% received a postnatal health check within 2 days following birth [10]. Health behaviors and care-seeking practices differ markedly between urban/rural areas and are underpinned by high rates of illiteracy (41% of women, 18% of men) and poor access to mobile phones among women [10]. In 2015, 19% of rural and 50% of urban women reported having access to a mobile phone [10].

### Trial enrollment

Trial inclusion will be restricted to women who are 12–34 weeks of gestation at randomization, ≥ 18 years of age, speak and understand Hindi, and own or have access to a mobile phone during the morning and afternoon. Women will be excluded who are BSNL mobile subscribers (due to poor network coverage) and do not provide consent to participate in the trial.

To identify eligible women, all FLHWs in the study villages will be contacted to obtain a list of the currently pregnant women in their village. If the FLHW is not available, a census of those villages will be carried out to find women greater than 18 years of age, within the fifth to seventh month (12–34 weeks of gestation at randomization) of their pregnancy. Women who complete the face to face survey and consent to receive Kilkari messages will be randomized to receive Kilkari calls (intervention) or not receive messages (comparison). Intervention area participants will start to receive Kilkari calls by no later than 8 months (34 weeks) after conception. The timing of this enrolment is intended to mirror that observed in other state deployments of Kilkari which rely on the identification of pregnant women via the MCTS/RCH database and in practice therefore enroll women in the later stages of pregnancy and/or early postpartum.

### Allocation and randomization

Gestational age, parity, age of woman, and ownership of phone are important variables potentially associated with exposure (listening to messages) and are likely to influence outcomes. The sample will be stratified by the above variables to allow for equal numbers of these categories in the sample between intervention and control groups (balance of covariates in the sample). Randomization will be performed using the *sample* command in stata with the use of the above listed variables as stratifiers. The randomization procedure will be done in blocks (block randomization) after the enrollment is completed for each sub-district administrative unit called as Community Development Block. This is to ensure a similar number of intervention and control subjects for each Community Development Block.

### Sampling

Table 2 summarizes the sample size requirements by activity, along with underpinning assumptions. To determine changes in RMNCH knowledge, practices, and careseeking over time (study aim 1), sampling will be powered to detect changes in coverage across study arms. To detect a 5% difference in reported practice of exclusive breastfeeding assuming an alpha of 0.05, 80% power, the estimated sample size for a two-sample proportions test would be 3200 women. After adjusting for a design effect (variance inflation factor) of 1.25 due to clustering at the level of the Community Development Block and a 20% loss to follow-up from enrollment to endline surveys and a potential loss of 35% of women due to poor reporting of phone numbers and/or changes to original phone numbers provided, a total of 5000 women will be enrolled to the study. Assuming 40% of women have access to a mobile phone, we anticipate that nearly 700,000 households will be listed in all four districts of MP.

**Table 2 Tab2:** Sample size estimates by study aim

Study aim	Survey	Target population	Sample size	Assumptions
Study aim 1a*	Face to face survey to measure changes in infant feeding practices	Women 5–7 months pregnant in four districts of MP	5000	• 5% change in reported practice of immediate and exclusive breastfeeding • Loss to follow-up of 20% from enrolment to final follow-up visit • Variance inflation factor of 1.25
Study aim 1b	Phone survey to measure changes in infant feeding	Postpartum women randomized to Kilkari	5000	Descriptive survey; administered to all women enrolled into the study
Study aim 1c*	Test-retest	Women 5–7 months pregnant in four districts of MP	168 women to be interviewed twice	• Proportion of positive responses of 0.35 for rater 1 and 0.40 for rater 2 • Adjusting for a 15% loss to follow-up/refusal between the first and second surveys
Study aim 1*	Phone survey for postpartum women: infant feeding, essential newborn care, RMC during childbirth	Women 1–4 months postpartum in two districts of MP	880 women interviewed as part of face to face surveys contacted to yield 146 completed face to face and phone survey interviews	• 20% phone survey response rate • Proportion of positive responses of 0.35 for rater 1 and 0.40 for rater 2
Study aim 2*	Phone survey for pregnant women: RMC during pregnancy	Women 5–7 months pregnant in four districts of MP	880 women interviewed as part of face to face surveys contacted to yield 146 completed face to face and phone survey interviews	• 20% phone survey response rate • Proportion of positive responses of 0.35 for rater 1 and 0.40 for rater 2
Study aim 2	MCTS/RCH registration	• FLHWs • Block and district medical officers • Data entry officers	64 in-depth interviews, 24 focus group discussions, and 24 observations	
Study aim 4	User perceptions of Kilkari	• FLHWs: ASHAs, ANMs • Women enrolled to Kilkari and male phone owners	49 in-depth interviews and six focus group discussions	

*Sample estimates based on kappa of 0.80, alpha of 0.05, margin of error of 0.05%

Among pregnant women, a module on RMC during antenatal care will be integrated into the baseline assessment amongst the enrolled women. To measure RMC during childbirth, a total of 880 women with a birth outcome in the preceding 1 to 4 months will be interviewed. This sample size was designed to accommodate inter-modal testing and is sufficient to additionally measure the prevalence of the RMC indicator of reported verbal abuse during childbirth with 80% power, alpha of 0.05, and precision of 5%.

To generate validated phone survey tools for RMC, we will aim to determine the inter-modal reliability of face to face versus computer-assisted telephone interviewing (CATI)/phone surveys for both pregnant and postpartum women. Assuming a kappa of 0.80, a margin of error of 0.05, an alpha of 0.05, and the proportion of positive responses of 0.35 for rater 1 and 0.40 for rater 2, 146 participants who have completed the survey are required. Adjusting for a 20% loss to follow-up between the face to face women’s survey and the following mobile phone survey, and a 20% baseline completion percentage for the latter, 880 women with a birth outcome in the preceding 1 to 4 months will be interviewed face to face. Within 1–2 weeks of the initial interview, a random sample of those completing the face to face interview who consent to be called for the follow-up phone survey will be contacted. Assuming a 20% response rate, all 880 women will be contacted as part of the phone survey to yield the 146 completed face to face and phone survey interviews.

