### Analyses

The statistical analysis plan will ensure that the analyses are not data driven or selectively reported. The presentation of primary analyses is expected in spring 2020, after all participants have been followed up to 1 year postpartum. Unadjusted and adjusted results will be presented as appropriate effects sizes with 95% confidence intervals (CI). Demographic and population characteristics of the women at baseline will be compared between study groups. Significance tests will be performed to investigate for differences between groups at baseline. Categorical outcomes will be analyzed using contingency tables and chi-square test. Continuous normally distributed variables will be analyzed using *t*-tests and non-normally distributed variables using non-parametric tests. The primary outcomes, early and exclusive breastfeeding and the adoption of modern contraception at 1 year postpartum, will be analyzed by intention-to-treat methodology, with adjustment for stratifying and baseline factors, including gestational age at enrollment, ownership of mobile phone, age of the pregnant woman at enrollment, and birth order of index pregnancy. Binary logistic regression (BLR) models with generalized estimation equations will be used to account for clustering effects at the level of the Community Development Block. The secondary outcomes of interest are anticipated to include immediate breastfeeding, skilled attendance and facility delivery, postnatal care, newborn birth practices, and immunizations. Binary logistic regression will be used for binary outcomes, and multiple linear regression will be used for continuous measures. Wilcoxon rank sum test will be used for continuous measures which are not normally distributed, including duration of breastfeeding. Cox proportional hazards regression will be used for time to event analyses, including time to initiation of breastfeeding and adoption of a modern contraceptive method in the postpartum period. All regression analyses will be performed with adjustment for baseline factors.

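### Women are randomized individually within Community Development Blocks, so the block is a stratum: the 1.25 design effect does not follow from the design, and block should be a stratification factor in the primary model

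*Protocol article*

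**What the plan says.** The Study design section sets the unit of randomization: "The study is an individually randomized controlled trial (iRCT) with a parallel, partially concurrent, and unblinded design". The Allocation and randomization section carries out allocation separately for each Community Development Block once enrolment there has closed, and gives the purpose: "This is to ensure a similar number of intervention and control subjects for each Community Development Block". Gestational age, parity, age and phone ownership are the other stratifiers.

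The Sampling section starts from 3200 women and applies a "design effect (variance inflation factor) of 1.25 due to clustering at the level of the Community Development Block". Table 2 repeats the 1.25. No intracluster correlation, number of blocks or derivation is given.

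In the Analyses section the primary outcomes are adjusted for stratifying and baseline factors. The list names gestational age, phone ownership, age and birth order, and is introduced as non-exhaustive. Block is not on it. Block appears only where "generalized estimation equations will be used to account for clustering effects at the level of the Community Development Block".

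**The concern.** A design effect above 1 for clustering belongs to designs in which whole clusters go to one arm, so that cluster differences become part of the arm difference. Here every block contributes similar numbers to both arms. A block with high breastfeeding prevalence raises both arms alike, and its level drops out of the contrast. The reason given for 1.25 therefore does not match the allocation.

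Two things are at stake. The sample-size statement, and any reading of power from it, contains a factor that the stated reason does not support. And the one role given to block in the primary analysis makes the standard error depend on an unstated number of clusters, which randomization by individual does not require.

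**Working it through.** **Inputs.** Control prevalence: "The control arm is expected to have a prevalence of 58% for the exclusive breastfeeding indicator". Effect: "To detect a 5% difference in reported practice of exclusive breastfeeding", read as 5 percentage points, so 63%. Error rates: "assuming an alpha of 0.05, 80% power", taken as two-sided. Base size 3200, loss to follow-up 20% and enrolment 5000 are from Sampling and Table 2. The number of blocks is not given; the study covers four districts, and 4 to 40 blocks is assumed.

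**1. Reproduce the plan's figure.** 3200 × 1.25 / (1 − 0.20) = 5000, exactly. Without the factor, 3200 / 0.80 = 4000. The 35% phone-number loss named in the same sentence is not in this product.

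**2. Design effect.** If whole blocks were randomized, the factor would be 1 + (m − 1) × ICC, with m women per block. With 4000 analysed, 1.25 corresponds to:
- 8 blocks (m = 500): ICC = 0.25 / 499 = 0.0005
- 20 blocks (m = 200): ICC = 0.25 / 199 = 0.0013
- 40 blocks (m = 100): ICC = 0.25 / 99 = 0.0025

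With individuals randomized 1:1 inside blocks and a constant effect, the factor is about 1 − ICC. At those same ICCs it is 0.997 to 1.000. Simulated variance ratios (4000 analysed, block intercept SD 0.3 on the logit scale, assumed) were 0.97 to 1.01 for 4 to 40 blocks.

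**3. Power.** 5000 × 0.80 = 4000 completers, 2000 per arm. The pooled prevalence is 0.605.
- No factor: SE under the null = √(2 × 0.605 × 0.395 / 2000) = 0.01546; SE under the alternative = √((0.58 × 0.42 + 0.63 × 0.37) / 2000) = 0.01544. z = (0.05 − 1.96 × 0.01546) / 0.01544 = 1.276, so power is 89.9%.
- Factor 1.25: effective 2000 / 1.25 = 1600 per arm. z = (0.05 − 1.96 × 0.01728) / 0.01726 = 0.934, so power is 82.5%.

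**4. Block-clustered GEE.** Null trials were simulated as in step 2, 4000 per setting, with independence working correlation and a nominal 5% test.

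| Blocks | Uncorrected sandwich SE / true SE | Type I error |
|---|---|---|
| 4 | 0.80 | 17.9% |
| 8 | 0.91 | 11.1% |
| 12 | 0.94 | 8.9% |
| 20 | 0.97 | 6.9% |
| 28 | 0.96 | 6.8% |
| 40 | 0.97 | 6.3% |

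Multiplying the variance by k/(k − 1) and referring to t on k − 1 degrees of freedom gave 4.7–5.4%. Treating women as independent gave 4.4–5.4%. Under different assumptions (beta-binomial block effects, ICC 0.01–0.05, identity scale) the uncorrected sandwich gave about 9–11% at 8 to 12 blocks, 6–7% at 20 to 30 and 5% at 40. An analysis stratified by block gave 4.2–5.7% throughout.

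**5. What could justify 1.25.** If the log odds ratio varies between k blocks with SD τ, the factor is roughly 1 + (τ² / k) / V, where V = 0.0641² = 0.0041 is the individual-level variance. At an assumed τ of 0.15 the simulated factors were 1.62 (8 blocks), 1.27 (20) and 1.09 (40). Solving for 1.25 gives τ = √(0.25 × k × 0.0041), or about 0.09, 0.14 and 0.20 at 8, 20 and 40 blocks. For scale, 58% versus 63% is a log odds ratio of 0.532 − 0.323 = 0.21.

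**The case against.** The case on the other side is substantial, and much of it stands.

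- **The factor does no harm to power.** This stands. It raises enrolment from 4000 to 5000. A reader might infer that 1000 women could be dropped. The protocol does not support that: applying its own 35% phone-number loss without the design effect gives 3200 / (0.80 × 0.65) = 6154. That omission is a separate problem, and any power shortfall it causes is not due to the handling of blocks.
- **The treatment effect may differ between blocks.** This is plausible, since the protocol describes geographic differences in phone access and network coverage as a barrier to receiving calls. Step 5 shows that such variation could produce a factor of 1.25. But the protocol does not argue it; the only reason it gives is clustering.
- **The standard errors have not been shown to be too small.** This also stands. A reader might infer that the planned GEE will reject too often. That needs both few blocks and an uncorrected sandwich variance. The protocol states neither, and the analysis plan, which is not shown, may specify a correction.
- **Block is not ignored.** A reader might infer that the analysis disregards a stratum. The adjustment list is open-ended, and because both arms sit in every cluster, the sandwich variance already reflects the cancellation within blocks. What remains is that clustering is the only role the text gives to block.

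**Conclusion.** The point holds in a limited form. The block is a randomization stratum, and clustering at that level does not inflate the variance of the arm contrast. With a treatment effect constant across blocks the design effect is about 1, not 1.25. The discrepancy is conservative: about 90% power rather than 82.5% at 4000 completers, assuming 58% versus 63%, a two-sided 0.05 test and 20% loss only.

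The type I error point is a conditional risk. It is material at about 12 blocks or fewer with an uncorrected sandwich (about 9–11% at 8 to 12 blocks, and higher in the extreme of one block per district), modest at 20 to 40, and absent if a small-sample correction is used. These figures rest on assumed block counts and between-block variation.

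**What to change.** 1. Include Community Development Block as a stratification factor in the primary model, together with the four listed stratifiers.
2. If block-clustered GEE is kept, as primary or sensitivity analysis, state the number of blocks and use a small-sample correction, for example k/(k − 1) with t on k − 1 degrees of freedom.
3. Either replace 1.25 by 1.0, or justify it by the expected variation of the treatment effect between blocks. Restate power accordingly, without reducing enrolment on this ground.

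The cost is wording and one model term; no new data are needed. There is one small downside: adjusting for block makes the odds ratio conditional on block, which should be said when it is reported. If inference is meant to reach beyond these blocks, the corrected GEE is the more suitable companion, since individual-level standard errors do not reflect effect variation between blocks.

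### The enrolment target of 5000 is described as allowing for a 35% phone-number loss, but the arithmetic and Table 2 leave it out; whether 80% power holds depends on what that loss means

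*Protocol article*

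**What the plan says.** The calculation is in the Sampling section of the protocol article. Its aim is "To detect a 5% difference in reported practice of exclusive breastfeeding", "assuming an alpha of 0.05, 80% power", and on that basis "the estimated sample size for a two-sample proportions test would be 3200 women". The Primary research hypothesis section supplies the control figure: "The control arm is expected to have a prevalence of 58% for the exclusive breastfeeding indicator".

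The Sampling text then names three adjustments to the 3200:
- a "design effect (variance inflation factor) of 1.25 due to clustering at the level of the Community Development Block";
- a 20% loss to follow-up between enrolment and endline;
- a "potential loss of 35% of women due to poor reporting of phone numbers and/or changes to original phone numbers provided, a total of 5000".

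Table 2, in the row for study aim 1a, gives the same 5000. For losses and clustering it lists only "Loss to follow-up of 20% from enrolment to final follow-up visit" and the variance inflation factor of 1.25. The 35% does not appear there.

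Two other statements bear on what the 35% could mean. The Analyses section says: "The primary outcomes, early and exclusive breastfeeding and the adoption of modern contraception at 1 year postpartum, will be analyzed by intention-to-treat methodology". The Measurement section, under study aim 1, makes the endline interview face to face in both arms.

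**The concern.** The text and the table give different accounts of what the 5000 contains, and the text's account fails its own arithmetic. A reader of the Sampling section would believe the trial has a margin against failed phone numbers. This is a risk the protocol takes seriously: Table 3 lists inactive and wrong numbers among the points where users drop out, and the Discussion describes an earlier messaging programme in which poor delivery would probably have hidden any effect.

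The article also does not say how a failed number would act on the primary comparison. It could remove outcome data, which shrinks the analysed sample. Or it could mean that the calls never arrive while the woman is still interviewed, which leaves the sample intact and may weaken the intention-to-treat effect. These have different consequences for power, and the stated 80% cannot be checked until one is chosen.

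**Working it through.** **Inputs.** Control 58% (Primary research hypothesis); difference 5 percentage points, alpha 0.05, power 80%, base total 3200, design effect 1.25, losses of 20% and 35%, target 5000 (Sampling). Two assumptions: alpha is two-sided, because sidedness is not stated; allocation is 1:1, from the aim of similar arm numbers in the Allocation and randomization section.

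**Step 1: reproduce the 5000.**
3200 × 1.25 = 4000; 4000 / (1 − 0.20) = 5000 exactly. These are Table 2's two adjustments, and they use up the whole figure.

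**Step 2: apply all three adjustments.**
- 20% contained within the 35%: 4000 / 0.65 = 6154
- Losses multiplied: 4000 / (0.80 × 0.65) = 7692
- Losses added: 4000 / (1 − 0.55) = 8889

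All exceed 5000. The base of 3200 has a little slack, since 58% versus 63% needs 1500 per arm, or 3000 in total. That does not close the gap: even from 3000, the most lenient case is 3000 × 1.25 / 0.65 = 5769.

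**Step 3: power at 5000 enrolled.** With n per arm = (women analysed / 1.25) / 2, d = p2 − p1 and p̄ the mean of p1 and p2:

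power = Φ{ [d√n − 1.96√(2p̄(1−p̄))] / √(p1(1−p1) + p2(1−p2)) }

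For 58% versus 63%, p̄ = 0.605. The second term in the numerator is 1.96 × √0.47795 = 1.355 and the denominator is √(0.2436 + 0.2331) = 0.690.

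| Meaning of the 35% | Women analysed | Effective total | n per arm | d√n | Power |
|---|---|---|---|---|---|
| No effect on outcome data or on the 5 points | 5000 × 0.80 = 4000 | 3200 | 1600 | 2.000 | 82.5% |
| Total outcome loss (20% inside it) | 5000 × 0.65 = 3250 | 2600 | 1300 | 1.803 | 74.2% |
| Outcome loss, multiplied with the 20% | 5000 × 0.80 × 0.65 = 2600 | 2080 | 1040 | 1.612 | 64.5% |
| Outcome loss, added to the 20% | 5000 × 0.45 = 2250 | 1800 | 900 | 1.500 | 58.3% |

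The difference detectable with 80% power is 6.0 points in the third row and 6.4 points in the fourth.

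**Step 4: the dilution case.** Suppose the 35% are interviewed at endline but get no calls, and suppose the 5 points applies only to women who are reached. The second supposition is not stated in the documents. The intention-to-treat difference is then 0.65 × 5 = 3.25 points, or 58% versus 61.25%. With 4000 analysed (3200 effective), d√n = 0.0325 × 40 = 1.300, the second term is 1.360 and the denominator 0.694, so power = Φ(−0.087), about 47%.

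**The case against.** A reader might infer that the trial simply lacks its stated 80% power. The documents do not support that as a flat statement. The endline is face to face, and the 20% already covers losses up to endline, so a failed phone number need not cost any outcome data. The hypothesis places the 5% between the two arms, which can be read as a contrast with non-receipt already built in. On that reading 4000 women are analysed and power is 82.5%. The text also calls the 35% a potential loss, and the Limitations section stresses the effort made to obtain correct numbers. All of this stands as an argument about power. It does not rescue the sentence: if the 35% has no bearing on the sample, it should not be listed as an adjustment that produced 5000.

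The dilution figure is open to the same challenge. The hypothesis speaks both of exposure to messages and of a difference between arms, so the wording does not settle whether 5 points is an effect in reached women. The 47% must carry that caveat.

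A reader might also infer that power passes 80% only if the 35% is ignored. That does not hold either. Taking 35% as the total loss and dropping the design effect gives 3250 analysed and 83% power (equivalently, 3200 / 0.65 = 4923, below 5000). There is a case for dropping it, because women are randomized individually within each Community Development Block. But it contradicts the 1.25 given in both the text and Table 2, so it cannot explain the stated figure.

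Finally, the planned exposure data and per-protocol analyses would help readers interpret a null result. They do not restore power.

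**Conclusion.** The statement that 5000 allows for the 35% is wrong as written. The 5000 reproduces exactly from the 1.25 and the 20% alone, Table 2 agrees with that, and from the stated base of 3200 the combinations that keep all three adjustments need between 6154 and 8889 women.

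The power consequence is conditional. With the 1.25 kept, and assuming 58% versus 63%, two-sided 0.05 and equal arms, it runs from 82.5% (no bearing on outcome data or on the between-arm effect) through 74% and 64.5% to 58% (added outcome loss). About 47% applies only under the undocumented assumption that the 5 points belongs to reached women. It is not established that the trial falls short of 80%. What is established is that the article claims an allowance it does not have, and that the stated power cannot be confirmed until the 35% is defined.

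**What to change.** 1. Correct the Sampling sentence to say that 5000 covers the design effect of 1.25 and the 20% loss only, in line with Table 2.
2. State whether the 35% means loss of outcome data or non-receipt of calls among women who are still interviewed and, if it is outcome loss, whether it includes the 20% or comes on top of it.
3. Restate power and detectable difference at 5000 enrolled under that meaning. If a dilution case is shown, label it as resting on the assumption that the 5 points applies to reached women; if the 5 points is instead the average over all randomized women, say so.

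The cost is a corrected sentence and a short power table. Enrolment, design and analysis do not change. Depending on the meaning chosen, the stated power may become less favourable.
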